### Intervention procedures

2.4.

The ten intervention sessions will be held over 2 consecutive weeks, with five sessions per week (Monday to Friday). Upon arrival to the session, the participants and guardians will be oriented and prepared to undergo the intervention. The electrodes will be positioned and the child will perform 20 min of neurofunctional training combined with tDCS. At the end of each session, the child will answer the questionnaire on adverse effects. Neurofunctional training associated with tDCS will be performed by two investigators. One investigator will be responsible for conducting the neurofunctional training and the other for the tDCS, ensuring that the electrodes remain properly positioned during the neurofunctional training. In addition, the tDCS equipment used indicates the quality of contact between the electrodes and the cranial surface and the maintenance of current flow, indicating the intensity applied throughout the intervention period. Therefore, even minimal changes can be easily identified.

Transcranial direct current stimulation: Transcranial stimulation will be administered using the tDCS device (Soterix Medical Inc., USA) with two sponge (non-metallic) surface electrodes (5 × 7 cm2) moistened with saline solution. The children will be randomly allocated to three types of treatment: 1) anodal tDCS over the primary motor cortex; 2) anodal tDCS over the cerebellum; and 3) sham tDCS. Following the 10–20 International Electroencephalogram System (77), the group to receive anodal tDCS over the primary motor cortex will have the anode positioned over Cz and the cathode positioned over the right deltoid muscle, whereas the group to receive anodal tDCS over the cerebellum will have the anode positioned one centimeter below the inion and the cathode positioned over the central supraorbital region (47). For sham stimulation, all electrode placement procedures will be performed using the montage over the primary motor cortex.

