Neurofunctional training: The training was carried out in a therapy room organized specifically for the intervention. Composed of postural control training and gait training. Immediately after the onset of tDCS (active or sham), the three groups will perform neurofunctional training consisting of postural control exercises and treadmill training conducted by a trained, experienced physiotherapist, with the participants performing the intervention individually. The 20 min of intervention will be divided into two steps (10 min each).Treadmill training: The training was performed on a Inbramed treadmill (Milenium ATL model, RS, Brazil). The treadmill training speed will be established based on the performance of the child in each session. Ideal speed will be the maximum speed at which the child is able to walk with adequate support of the feet upon initial contact and throughout the entire support phase of the gait cycle. The speed will be gradually increased during the initial two minutes and gradually reduced during the final two minutes, maintaining a constant speed in the interim. During training, the children used their habitual shoes, which were duly placed by the physiotherapist. The therapist remained behind the participants, facilitating gait training if necessary and ensuring both the safety of the intervention and the best possible movement kinematics. Throughout treadmill training, the therapist in charge also provided verbal commands to the participant to improve the execution of gait (48, 78).Postural control exercises: The second step will involve a circuit of activities based on the tasks of the MABC-2 to favor the improvement in postural control. The activities will be four exercises performed for 40 s with a 20-s rest interval. The four exercises will be selected individually according to the performance of each child during the MABC-2. Items from the balance and aim subscale will be defined as circuit exercises, which the child is able to perform with a delay (does not reach the complete performance of the item) and with qualitative observations in aspects of posture/body control. Some examples of activities are: balancing on one foot, walking on tiptoes, jumping, etc. During the execution of the circuit activities, the physiotherapist will remain beside the child, guaranteeing his/her safety in the face of imbalance and offering verbal commands with motivational phrases and guidance for the steps of the activities. Each participant will perform two complete circuits, with a two-minute rest interval between circuits.

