## Discussion

3.

Motor training combined with tDCS has been shown to be safe, viable and effective for children and adolescents with motor control disorders. Considering the results available in the scientific literature demonstrating the promising effects of anodal tDCS in children with ASD, especially aspects related to communication and behavior, it is of interest to expand the knowledge regarding the effects of tDCS also on motor skills in this population. If demonstrated that anodal tDCS administered over areas of the brain involved in motor control, such as the primary motor cortex and cerebellum, can enhance the effects of gait and balance training in only ten sessions in two consecutive weeks, the clinical applicability of this stimulation modality will be expanded as well as more scientifically founded.

Although abnormalities in gait and balance are not primary characteristics of ASD, such abnormalities compromise independence and global functioning during the execution of routine activities of childhood. Motor rehabilitation poses a challenge for therapists, families and patients, as children with ASD are often enrolled in behavioral treatment programs that require a considerable number of intervention hours per day. Thus, therapeutic possibilities with execution in focused, short-term programs that prove effective could be a favorable option for the treatment of abnormalities in motor skills.

Therefore, the present protocol for a randomized controlled clinical trial involves assessment measures of results with representativeness in the daily activities of children. Motor skills will be assessed using the MABC-2, which consists of items that measure gross and fine motor skills, to determine whether motor training (gait and balance) combined with anodal tDCS achieves positive results not restricted to the motor task being trained. Scales and tests will be used to measure the effects on mobility and balance during functional activities, such as walking, standing up, sitting down, changing direction, etc. These assessment tools will enable the understanding of the effects on an important domain of the International Classification of Functioning, Disability and Health – ACTIVITY, which is the primary focus of the proposed intervention.

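### The MABC-2 total and balance scores cannot show benefit beyond the trained task, because the training circuit draws on MABC-2 balance and aiming items; manual dexterity could

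*Protocol article*

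**What the plan says.** Section 2.4 (Intervention procedures) divides each 20-minute session into treadmill training and "a circuit of activities based on the tasks of the MABC-2 to favor the improvement in postural control". On content: "The four exercises will be selected individually according to the performance of each child during the MABC-2". The source is explicit: "Items from the balance and aim subscale will be defined as circuit exercises", namely items "which the child is able to perform with a delay (does not reach the complete performance of the item"), with qualitative observations on posture and body control. On dose: "The activities will be four exercises performed for 40 s with a 20-s rest interval"; "Each participant will perform two complete circuits, with a two-minute rest interval between circuits"; "The ten intervention sessions will be held over 2 consecutive weeks, with five sessions per week". All three groups receive this training.

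Section 2.2 (Participants) bases the sample size on the MABC-2 total and balance scores as the primary clinical results. Section 2.3.2.1 (Primary outcome) gives balance as the principal reason for using the battery. It lists three categories (manual dexterity, aiming and catching, balance) and three balance items per age group.

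The Discussion (section 3) says the MABC-2 will serve to determine whether training plus anodal tDCS "achieves positive results not restricted to the motor task being trained". It describes the trained task there as gait and balance.

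**The concern.** The Discussion relies on the MABC-2 to show that benefit extends past what was practised, yet part of what is practised comes from the MABC-2 itself. Exercises are chosen from a child's weaker items on the battery, rehearsed, and the same battery is then scored as the primary outcome. A higher total or balance score may therefore reflect better performance of rehearsed items, broader motor improvement, or both.

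What is at stake is how a positive result would be described. If active tDCS beats sham on the total or balance score, the Discussion as written invites the conclusion that the effect generalises, and those scores cannot show that. The same holds for within-group gains, which the Introduction and section 2.9 (Expected results) predict in all three arms.

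**Working it through.** **1. The plan's own timing reproduces.** Inputs from section 2.4: four exercises, 40 s each, 20 s rest, two circuits, 2 min between circuits.
- One circuit: 4 × (40 + 20) s = 240 s = 4 min.
- Step length: 2 × 4 min + 2 min = 10 min, which matches the 10 minutes allotted to this step.

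**2. Amount of circuit practice.**
- Per session: 4 × 40 s × 2 = 320 s.
- Over ten sessions: 320 s × 10 = 3,200 s, about 53 min.
- Per exercise: 2 × 40 s = 80 s per session. This would be 80 × 10 = 800 s over the course only if the same four exercises were kept throughout, which the protocol does not state.

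**3. How much of the battery is exposed.** Inputs from sections 2.3.2.1 and 2.4.
- Categories supplying exercises: balance and aiming, so 2 of 3.
- Balance has 3 items per age group and 4 exercises are chosen. If the four are based on different items, at most 3 come from balance and at least 4 − 3 = 1 comes from aiming.
- A child's circuit can therefore cover the whole balance subscale. Nothing says that it does so in every child.

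**4. What each score can show.**

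| Score | Circuit exercises drawn from it? | What an active-versus-sham difference supports |
|---|---|---|
| Balance | Yes, up to all three items | tDCS enhances performance on trained tasks |
| Aiming and catching | Yes | As above |
| Manual dexterity | No | Benefit beyond the trained task |
| Total | Mixed | Cannot be divided between trained and untrained content |
| Pediatric Balance Scale | No, but same domain (balance) | Near transfer at most |

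The Discussion's description of the trained task leaves out aiming, so a reader of that section alone would count aiming and catching as untrained. Section 2.4 shows that it is not.

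**5. Power for manual dexterity.** The protocol gives no effect size for this category, so a range is assumed. For a two-sided two-sample t-test at 5% with n per arm and standardised difference d, power = P(|T| > t(0.975, 2n − 2)), where T is noncentral t with 2n − 2 degrees of freedom and noncentrality d√(n/2).

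| Assumed d | n = 8 per arm | n = 10 per arm |
|---|---|---|
| 0.5 | 15% | 19% |
| 0.8 | 32% | 40% |
| 1.0 | 46% | 56% |
| 1.39 (section 2.2 figure) | 73% | 84% |

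These are single pairwise comparisons without adjustment. The planned Tukey procedure over three groups would give less. The point does not alter the sample size.

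**The case against.** The main goal in the Introduction is to compare motor cortex, cerebellar and sham stimulation on top of identical training, and the hypothesis is that active stimulation enhances that training. An outcome close to the trained tasks suits that question, and the Introduction itself says motor results follow the type of training. Transfer is not among the stated objectives and appears in one Discussion sentence. That sentence can be read as pointing to the fine-motor part of the battery, which is untrained. Category-level reporting is also commonly left to an analysis plan.

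Most of this stands and limits the point to interpretation. What remains is that the sentence assigns the transfer question to the MABC-2 as a whole, the only scores named as primary results are total and balance, and no category is tied to the claim. This is a mismatch between two statements in the document and does not depend on anything left to an analysis plan.

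A reader might also infer more than the text supports:
- **That rehearsal confounds the primary comparison.** It does not, because all arms train alike.
- **That children practise items they failed.** Section 2.4 describes items performed with delay or incompletely, and activities based on the test tasks.
- **That practice inflates age-normed scores by a known amount.** The documents give no basis for sizing this. Practice is planned equally in every arm, so any such effect bears on within-group change.

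**Conclusion.** The point holds as a limit on interpretation. The design, the primary outcome, the active-versus-sham test and the sample size all stand. The Discussion's claim of benefit beyond the trained task is not supported by the total or balance score, because two of three categories supply circuit exercises and up to the whole balance subscale may be practised. Manual dexterity is the only category from which no exercise is drawn, and it is already part of the battery.

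This rests on reading the aim subscale in section 2.4 as the aiming and catching category, and on exercises based on MABC-2 tasks being close enough to the scored items to count as practice of them. The effect on the scores cannot be quantified from the document. It is a modest matter, worth correcting because the correction is cheap.

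**What to change.** Keep the training and the primary outcome as they are, and make two changes.

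1. Pre-specify the between-arm comparison of the manual dexterity category as the evidence for benefit beyond the trained task. The Pediatric Balance Scale may be cited as near-transfer support only.
2. Reword the Discussion. Suggested text: *Because circuit exercises are based on MABC-2 balance and aiming items, differences or within-group gains in the total and balance scores will be interpreted as performance on trained tasks. Benefit beyond those tasks will be judged from manual dexterity.*

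Recording which exercises each child trained is optional and should be descriptive only. Trained items are chosen for poor initial performance, so a trained-versus-untrained split would be affected by regression to the mean. The items also differ by child and age band, and each arm has only 8 to 10 children. The document does not say that item-level scores are kept, so this step might need extra data capture.

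The cost of the two main changes is wording and one named comparison. The drawback is that the transfer claim rests on a narrower score with low power unless the effect is large, so a null result on manual dexterity should not be read as showing no transfer.

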
### Statistical analysis

2.5.

The precision of all data will be verified by two researchers and a blinded statistician will conduct all analyses. The Kolmogorov–Smirnov test will be used to determine the distribution of the data regarding adherence to the Gaussian curve. Parametric data will be expressed as mean and standard deviation or 95% confidence interval. Nonparametric data will be expressed as median and interquartile range. Two-way analysis of variance (ANOVA) followed Tukey’s *post hoc* test will be used to assess the effects of tDCS on the outcome variables. For all analyses, the fixed independent variables will be group (active tDCS over the primary motor cortex, active tDCS over the cerebellum and sham tDCS) and assessment time (pre-intervention, post-intervention, follow-up 1 and follow-up 2). The dependent variables will be the outcomes studied. The effect size (Cohen’s d) will be calculated from the difference in the values obtained during the pre-intervention, post-intervention, first follow-up and second follow-up assessments comparing the three groups. Predictive response factors will be identified through logistic regression analysis. Logistic regression models will be performed with the outcomes: type of daily medication, ASD severity, MEP (presence or absence) and pre-intervention MABC-2 result. The level of significance will be set at 5% (*p* < 0.05) and Statistical Package for the Social Sciences (SPSS, version 21.0) will be used for the analyses.

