**Methods and design:**

A randomized, sham-controlled, double-blind clinical trial will be conducted involving 30 children with ASD that will be recruited to receive ten sessions of sham or ten sessions of active anodal tDCS (1 mA, 20 min) over the primary motor cortex or cerebellun combined with motor training. The participants will be assessed before as well as one, four and eight weeks after the interventions. The primary outcome will be gross and fine motor skills. The secondary outcomes will be mobility, functional balance, motor cortical excitability, cognitive aspects and behavioral aspects.

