#### Neurophysiological assessment measure

2.3.3.

Cortical excitability: Transcranial magnetic stimulation (TMS) will be used for the assessment of cortical excitability using a magnetic stimulator with a circular MagVenture coil. The response to stimulation applied to the motor cortex will be recorded in the thumb adductor and femoral quadriceps of both limbs to identify the motor evoked potential (MEP) and the motor cortical representation pattern (contralateral, bilateral or unilateral). The MEP responses will be filtered and amplified using a surface electromyograph. The signals will be transferred to a personal computer for offline analysis using data collection software. The motor threshold and MEP will be measured using the single-pulse TMS method. The motor threshold will be found in the region of the cortex with the lowest intensity necessary to generate a peripheral response. The same method will be employed to determine the MEP using 110% of the motor threshold intensity. Ten measures of the MEP will be performed in each assessment step.

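### The normality screen changes only the descriptive summary: every outcome is compared by the same Gaussian two-way ANOVA, which read literally includes a nominal TMS measure

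*Protocol article*

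**What the plan says.** Section 2.5 (Statistical analysis) opens with a normality check: the Kolmogorov–Smirnov "test will be used to determine the distribution of the data regarding adherence to the Gaussian curve". Its one stated consequence is the form of the summary. Variables judged Gaussian get a mean with SD or confidence interval; for the others, "Nonparametric data will be expressed as median and interquartile range".

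The treatment comparison does not depend on that result. Two-way ANOVA followed by Tukey's post hoc "test will be used to assess the effects of tDCS on the outcome variables". The scope is general: "For all analyses, the fixed independent variables will be group" and assessment time, and "The dependent variables will be the outcomes studied". No transformation, rank method or categorical method is named for comparing the groups. The logistic regression in the same section is for predictors of response.

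The abstract makes cortical excitability a secondary outcome: "The secondary outcomes will be mobility, functional balance, motor cortical excitability, cognitive aspects and behavioral aspects". Section 2.3.3 describes three TMS readouts: motor threshold, MEP, and "the motor cortical representation pattern (contralateral, bilateral or unilateral"). It adds: "Ten measures of the MEP will be performed in each assessment step".

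**The concern.** A screen is useful if something follows from it. Here a variable can be labelled nonparametric and shown as a median, and then be tested by a comparison of means. The reader would see one quantity and a p-value for another.

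Two TMS readouts are exposed.

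- **MEP amplitude** is positive and may be right-skewed. On the raw scale a few large values would then dominate the mean and the residual variance.
- **The representation pattern** is nominal, so a mean, a Tukey contrast or a Cohen's d has no meaning for it. Its categories also overlap, because a response on the contralateral side only is also unilateral.

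The Introduction attributes the expected benefit of active stimulation to its effect on cortical excitability, and the Discussion plans to relate MEP changes to motor results. A missed effect here would weaken the mechanistic reading of the trial. The primary MABC-2 analysis is not shown to be affected.

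**Working it through.** **1. What the screen controls.** Section 2.5, step by step:

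| Screen result | Summary shown | Test of treatment |
|---|---|---|
| Gaussian | mean with SD or CI | two-way ANOVA, Tukey |
| Not Gaussian | median, IQR | two-way ANOVA, Tukey |

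The last column does not change. The screen's power therefore has no bearing on which test is used.

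**2. Size per arm.** Section 2.2 gives a balance change of 2.4 with SD 1.70, so d = 2.4/1.70 = 1.41. By the normal approximation, two-sided 5% and 80% power, n = 2(1.96 + 0.84)²/1.41² = 7.9, so 8 per group and 24 in all. With 20% dropout, 24/0.80 = 30, or 10 per arm. The plan's figures reproduce and are not in dispute. I use 10 per arm below.

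**3. How the screen behaves.** Simulated rejection rates at the 5% level with estimated mean and SD. Lognormal data are an assumption.

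| Data tested | log-SD | Corrected critical value | Uncorrected |
|---|---|---|---|
| n = 10 | 0.5 | 18% | about 0.1–0.2% |
| n = 10 | 1.0 | 46% | 2.6% |
| n = 30 pooled | 0.5 | 49% | 4% |
| n = 30 pooled | 1.0 | 94% | 43% |

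Section 2.5 states neither the correction nor whether groups are tested separately. If the corrected test were run in each of 3 × 4 = 12 group-by-time cells, and the cells were independent, truly normal data would be flagged at least once with probability 1 − 0.95¹² = 46%. This affects only which summary is printed.

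**4. Cost of the raw scale for MEP amplitude.** All inputs other than n are assumptions:

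- lognormal values with log-SD 0.5 or 0.8;
- 10 per arm, one time point;
- a shift of 1.39 log-SD, the protocol's MABC-2 effect size borrowed for MEP;
- Tukey comparison of one active arm with sham, 40,000 simulated trials.

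| Scenario | Log scale | Raw, log-SD 0.5 | Raw, log-SD 0.8 |
|---|---|---|---|
| Both active arms rise | 73% | 52% | 35% |
| Only the tested arm rises | 73–74% | 73–74% | 65% |

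A shift of 1.39 log-SD multiplies a raised arm's raw SD by exp(1.39 × 0.5) = 2.0 or exp(1.39 × 0.8) = 3.0. When both active arms rise, two of the three arms inflate the pooled error variance. That explains the larger loss. The Introduction hypothesises benefit in both active arms, so the first row matches the protocol's expectation.

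**5. False positives.** With no effect and 3 × 10 lognormal values, the raw-scale overall F test rejects in 4.3%, 4.0% and 3.3% of trials at log-SD 0.5, 0.75 and 1. There is no inflation.

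**6. The pattern.** No arithmetic applies. Section 2.3.3 defines an unordered three-category measure within a secondary outcome domain, and Section 2.5 makes ANOVA on the outcomes studied the only treatment comparison.

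**The case against.** The best defence is that little of this is in the text. The documents do not say that MEP values are skewed, and averaging ten measures per assessment would reduce within-child skew. The 1.39 shift belongs to the MABC-2. The simulation uses a single time point, not the planned group-by-time model. The pattern is never named as an analysed outcome; the Discussion speaks only of the motor evoked potential. Methods for secondary measures are often left to a fuller plan.

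Most of this stands as a limit on size. The last point does not remove the problem, because Section 2.5 is not silent: it states one method for all analyses. Reading that rule onto the pattern is literal, but no other treatment comparison is offered for it.

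The documents do not support four stronger readings that a reader might infer:

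- **A weak screen sends skewed data into ANOVA.** The screen never selects the test, so a perfect one would change nothing.
- **The screen has almost no power.** That needs an uncorrected test run per group, and neither is specified.
- **The power loss is general.** It is large only if both active arms rise. With one arm raised at log-SD 0.5 it disappears.
- **Cortical excitability has no valid analysis.** Motor threshold is a third readout, and nothing here shows ANOVA to be unsuitable for it.

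**Conclusion.** The point holds as a defect of a stated rule. The normality step has no effect on inference, variables called nonparametric are still tested on means, and read literally a nominal measure with overlapping categories goes into ANOVA. The harm is possible loss of power and mismatched reporting for a secondary outcome, not false positives. Under assumed lognormal MEP amplitude, the loss is from about 73% to between 52% and 35% if both active arms rise. If one rises, it ranges from nothing to about 8 percentage points (73% against 65%). These figures depend on the assumed log-SD, shift and single time point. The finding about the rule itself does not. It should be corrected, but it does not threaten the primary comparison.

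**What to change.** Revise Section 2.5 as follows.

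- Remove the Kolmogorov–Smirnov step as a screen. Check model residuals graphically, and use the same summary statistic for a given variable in all groups.
- Analyse MEP amplitude on the log scale among children with a recordable MEP, and report ratios with 95% CI. Section 2.5 itself allows for absent MEPs, which have no logarithm, so handle absent responses in the categorical analysis below and report their number by group.
- Recode the representation pattern as contralateral only, bilateral, ipsilateral only or no response, and compare groups by an exact test.
- Log-transforming the test durations is optional, since the gain there is small.

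The cost is a few sentences and some recoding, with no extra data collection. The downside is that MEP effects are read as ratios and apply only to children with a recordable response.

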### Participants

2.2.

Thirty children will be recruited from the XXX Child Neurorehabilitation Clinic in the city of XXX, XXX. Participants will undergo detailed screening with the eligibility criteria for inclusion in the study.

The sample size was calculated considering the primary clinical results, which are the total and balance score of the Movement Assessment Battery for Children, 2nd ed. (MABC-2) (62). The calculation of the sample size was based on data from a study involving a group of individuals with ASD who received motor training combined with tDCS over the primary motor cortex (59). The estimated effect size of the previous study was 1.39 (change in total MABC-2 score of 16.5 with a standard deviation [SD] of 5.98; change in score of balance category of MABC-2 of 2.4, SD: 1.70; α = 0.05 (two-tailed) and β = 0.8). The estimate indicated a minimum of 24 participants (eight per group). Considering a possible dropout rate of 20%, 30 participants will be recruited.

The children will be screened for participation in the study based on the following:

Inclusion criteria: 1) Diagnosis of ASD confirmed though a clinical examination; 2) Standard neurobehavioral assessment that confirms and categorizes the severity of ASD; 3) Levels I, II and III according to the Diagnostic and Statistical Manual of intellectual disability (DSM-5); 4) Age three to eight years; 5) Sufficient response to understand simple verbal commands; 6) No change in medication in the six months prior to the onset of the study or during the study; 7) Signed statement of informed consent by a legal guardian; 8) Agreement to participate in study through term of assent.

Exclusion criteria: 1) Diagnosis of epilepsy or seizure within the 12 months prior to the onset of the study; 2) Neurological, neuromuscular disorders or syndromes other than ASD; 3) Having been submitted to orthopedic or neurological surgery within 12 months prior to the intervention; 4) Orthopedic deformities with indication for surgery; 5) Implants in the skull or having undergone some neurosurgical procedure; 6) Metallic implants in the head, neck, chest or upper limb; 7) Hearing devices; 8) Degree of cooperation incompatible with the adequate performance of the activities proposed in the present project.

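### The two-way ANOVA in section 2.5 names only group and time for outcomes measured four times on each child; followed as written, it uses the wrong error term for both the group and the group-by-time test

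*Protocol article*

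**What the plan says.** Section 2.5 (Statistical analysis) names one model for all outcomes: "Two-way analysis of variance (ANOVA) followed" by Tukey's post hoc test. It then lists the factors: "For all analyses, the fixed independent variables will be group" (three arms) and "assessment time (pre-intervention, post-intervention, follow-up 1 and follow-up 2". The significance level is 5%.

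The abstract confirms that the measurements are repeated on the same children: "The participants will be assessed before as well as one, four and eight weeks after the interventions". The visit schedule in section 2.1 agrees. Section 2.2 plans 30 children, 10 per arm, from a minimum of eight per arm.

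The article nowhere mentions repeated measures, a within-child factor, a random child effect, a covariance structure or a sphericity correction. Section 2.6 adds that missing post-intervention values will be filled from the previous observation.

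**The concern.** Group varies between children and time varies within them, so the two kinds of comparison need different error terms. A two-factor ANOVA without a child term has only one. It treats 30 children at four times as 120 separate observations.

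Two errors follow, in opposite directions, whenever a child's scores are positively correlated:

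- The group main effect is judged against too small an error with too many degrees of freedom. Chance differences between children can then look like differences between arms.
- The group-by-time interaction is judged against an error that still contains the stable differences between children. A real difference in improvement can then be missed.

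The second matters most for the trial's question. The pre-intervention assessment is one of the four levels of time, so the group main effect averages in values recorded before any stimulation. The tDCS effect therefore shows in the interaction. The model applies to the primary outcome and all others.

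**Working it through.** **Inputs.** From the article: 3 arms, 4 times, 10 children per arm, 5% level, effect size 1.39 ("The estimated effect size of the previous study was 1.39"). Assumed, because the documents do not give it: an exchangeable within-child correlation ρ, shown from 0.1 to 0.8. Also assumed: the two-way ANOVA includes the group-by-time term, and the effect is present in both active arms at all three later assessments.

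**The plan's own figure.** Section 2.2 gives "α = 0.05 (two-tailed) and β = 0.8", read here as 80% power. The balance figures give d = 2.4/1.70 = 1.41, and n = 2 × ((1.960 + 0.842)/1.41)² = 7.88, so 8 per arm, as stated. With 1.39 the same formula gives 8.12. The SDs quoted there accompany changes in score, so 1.39 is taken on the change scale.

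**Degrees of freedom.** 120 observations less 12 cell means leaves 108. This pools 3 × 9 = 27 between-child and 3 × 9 × 3 = 81 within-child degrees of freedom.

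**Expected mean squares with no effect** (total variance set to 1):

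- group: 1 + 3ρ
- group-by-time: 1 − ρ
- pooled residual: [27(1 + 3ρ) + 81(1 − ρ)]/108 = 1

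So the group F ratio centres near 1 + 3ρ and the interaction F ratio near 1 − ρ, where both should centre near 1. At ρ = 0.5 these are 2.5 and 0.5.

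**Power of the interaction test.** The change between two assessments has SD √(2(1 − ρ)), so the effect on the score scale is Δ = 1.39 × √(2(1 − ρ)). The squared deviations of the effect pattern sum to 2/3 over arms and 3/4 over times. The noncentrality is

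λ = 10 × Δ² × (2/3) × (3/4) / (1 − ρ) = 10 × 1.39² = 19.3, whatever ρ is.

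With a child term, F on 6 and 81 df (critical value 2.21) gives 91% power at every ρ. As written, the same numerator is divided by the pooled residual and compared with 2.18 (6 and 108 df). Drawing the mean squares from their chi-squared distributions (1,000,000 draws) gives:

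| ρ | Group test, type I error as written | Interaction, type I error as written | Interaction power as written | Interaction power with child term |
|---|---|---|---|---|
| 0.1 | 10% | 3.1% | 88% | 91% |
| 0.3 | 20% | 0.8% | 73% | 91% |
| 0.5 | 30% | 0.1% | 44% | 91% |
| 0.7 | 38% | <0.1% | 8% | 91% |
| 0.8 | 41% | <0.1% | 1% | 91% |

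Simulating whole trials gives the same figures to within about one percentage point. With child as the error stratum, the group test returns to about 5%.

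**Sensitivity.**

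- With 8 children per arm, interaction power at ρ = 0.5 is 29% as written against 81%.
- If 1.39 is read on the raw-score scale, λ = 10 × 1.39²/(2(1 − ρ)). Power is then 51% against 77% (ρ = 0.3), 44% against 91% (0.5) and 35% against 99% (0.7).
- If the correlation decays with time (first-order autoregressive, 0.7 to 0.9), the group test as written rejects 33% to 42% under the null. A split-plot interaction test without a sphericity correction runs at about 7% to 7.5%.

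**The case against.** The strongest reply is that two-way ANOVA on group and time is common shorthand for a repeated-measures ANOVA, and that a condensed article may leave the error structure to a fuller plan. The word fixed does not decide it, because group and time are fixed effects in a correct mixed model too. This stands as far as it goes: the article never says that the four assessments are independent, and a reader who infers that the authors intend this goes beyond the text. But the article gives the test, both factors, the post hoc procedure, the level and the software. The model is stated, and applying it literally gives invalid tests.

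Three further inferences are tempting but not supported:

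- *The interaction test always loses most of its power.* The loss depends on an undocumented correlation. At 0.3 it is about 18 points, at 0.5 about half the power, and only above that most of it.
- *Tukey's test runs over all 12 group-by-time cells.* Section 2.5 does not say which means are compared, so no penalty can be computed from it.
- *The trial will declare success on the group main effect.* The article does not say so. Its hypothesis concerns greater improvement, and its effect sizes use differences between assessments. The inflated group test does harm only if it is used for inference, which the current text leaves open.

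**Conclusion.** The point holds: the model as worded does not fit the design. For any positive within-child correlation the direction of both errors is certain; only their size is assumed. The group test runs at about 2 to 8 times its nominal level over correlations 0.1 to 0.8. The interaction test is conservative throughout, with a power loss that is small at 0.1 and severe at 0.7. Higher values are plausible for one test battery repeated within weeks, and carrying observations forward tends to raise them further.

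If a repeated-measures analysis was already intended, the defect is one of wording. If not, the group and group-by-time tests of every outcome are affected. The text must change in either case, before the data are analysed.

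**What to change.** In section 2.5, replace the two-way ANOVA by one of these:

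- a split-plot (repeated-measures) ANOVA with group between children, time within children and a sphericity correction; or
- a linear mixed model with fixed group, time and group-by-time terms and child as random effect.

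State that the tDCS conclusion rests on group-by-time contrasts: each active arm against sham, and motor cortex against cerebellum, at named assessments. Name the means that the post hoc test compares, and use the error term that matches those contrasts. If a repeated-measures ANOVA was already meant, say so explicitly.

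The cost is analysis wording only: no new data, visits or children.
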